## 6.4 Sample Size and Power

Assumptions of sample size calculations. Our sample size calculations are based upon our primary aims – to compare stone clearance and patients' experiences of treatment options to remove kidney stones. We use Bonferroni adjustment to allow for multiple comparisons, which is known to be conservative. The multiple comparisons are: difference in stone clearance across 3 treatment options and mean difference in PROs across 3 treatment options at 1 week, 3 weeks, 6 weeks, and 3-months after surgery. We assume a loss to follow up of 15%. We assume the propensity score model, which accounts for dependence of observations at the hospital and surgeon levels, controls for confounding such that patients whose propensity scores are equal have similar baseline covariates values. In the initial comparative effectiveness study, we anticipate enrolling approximately 750 patients in URS, 350 in SWL, and 100 in PCNL. As defined by Varadhan *et al.*, the goal of the proposed HTE analyses is descriptive: to report treatment effects for prespecified subgroups in accordance with a prospectively specified analytic strategy. Accordingly, descriptive HTE analyses need not be powered to detect heterogeneity because the goal is to report results for future synthesis.

**Aim 1:** 294 patients in SWL, 294 patients in URS, and 92 patients in PCNL will have 80% power to detect an expected difference of 80% vs. 65% in stone clearance between URS and SWL, and to detect a difference of 90% vs. 65% in stone clearance between PCNL and SWL at  $\alpha=0.05$ , accounting for multiple comparisons and loss to follow-up.

**Aim 2:** Minimal important differences for many PROMIS domains are in the range of 2 to 6. Assuming a 10% loss to follow-up, 39 patients in each group will have 80% power to detect an expected difference of 2 points in each of the 5 PROs across treatment options at  $\alpha=0.05$ , adjusting for multiple comparisons.

---

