### Outcome model

Both the primary and secondary outcomes were compared using the IPW approach. The outcomes were compared using regression models with IPW and adjusted for unbalanced confounders after weighting. The analysis of PROs was conducted at 1-week, 3-weeks, 6-weeks, and 3-months after the index surgery adjusting for baseline scores.

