| PROMIS Sleep Disturbances                                                                                                                                                                                                                                                                                                                                                                                                                                                | 0.47(0.38,0.56)          | -5.58(-9.77,-1.39)   | -5.27(-9.12--1.41)                          | 0.63(0.51,0.76)          | -5.12(-8.27,-1.96) | -3.17(-6.47-0.14)                           |
| PROMIS Stress Experiences                                                                                                                                                                                                                                                                                                                                                                                                                                                | 0.69(0.61,0.77)          | -11.19(-17.11,-5.27) | -11.56(-17.78--5.35)                        | 0.61(0.49,0.72)          | -1.01(-7.1,5.09)          | -1.18(-6.48-4.12)                           |
| Estimates with 95% confidence intervals not covering zero are bolded.
† The range of the Dysfunctional Voiding Symptom Score (DVSS) is 0 to 30.
‡ The range of the Questionnaire for Urinary Issues – Kidney Stone Surgery (QUIKSS) is 0 to 56. QUIKSS is comprised of 16 items that used a frequency response scale and a 7-day recall period. Each item was scored from never (0) to always (4). The total score was the sum of the items. |                          |                             |                                             |                          |                           |                                             |

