### 6.3.2 Analysis of Primary Outcome of Interest

**Stone Clearance: Overall Treatment Effect** The primary analysis of Aim 1 is to test the differences in stone clearance after surgery across treatment options. We will fit weighted logistic regression models for stone clearance measured at 6 weeks after surgery. We will use the likelihood ratio test to test the null hypothesis. We will report point estimates and 95% confidence intervals (CIs) of odds ratios in stone clearance between each pair of treatments.

**SubAim 1a: Heterogeneity of Treatment Effect (HTE).** We will add pairwise interactions between the treatment dummy variables and stone size and between treatment and stone location. We will also explore HTE by other patient participant characteristics including, but not limited to, ambulatory status.

**SubAim 1b: Effect modification by procedure-specific techniques.** We will stratify the data by treatments and, within each treatment, we will fit logistic regression models with random intercepts to test whether modifiable techniques improve stone clearance.

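### Section 6.4 sizes the study with a Bonferroni adjustment, but neither section 6.3.2 nor the SAP carries any adjustment or testing order into the analysis, so the stated family-wise error control is not delivered

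*Combined protocol and SAP*

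**What the plan says.** Section 6.4 of the protocol treats stone clearance and patient experience together as the primary aims for sizing. It says "We use Bonferroni adjustment to allow for multiple comparisons, which is known to be conservative" and lists the comparisons as "difference in stone clearance across 3 treatment options and mean difference in PROs across 3 treatment options at 1 week, 3 weeks, 6 weeks", with 3 months as the fourth time. For Aim 1 it prints "294 patients in SWL, 294 patients in URS, and 92 patients in PCNL will have 80% power", described as "accounting for multiple comparisons and loss to follow-up". The Aim 2 statement also says that it adjusts for multiple comparisons. The same section describes the heterogeneity analyses as descriptive and not powered.

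Section 6.3.2 plans a weighted logistic model and a likelihood ratio test of the overall null hypothesis, for which it gives no alpha. It continues: "We will report point estimates and 95% confidence intervals (CIs) of odds ratios in stone clearance between each pair of treatments". For PROs, the protocol plans separate models for each domain and time point and states no significance level. The protocol refers the detail of the methods to the SAP.

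The SAP's Outcome model section says only that outcomes were compared by weighted regression, and that "The analysis of PROs was conducted at 1-week, 3-weeks, 6-weeks, and 3-months after the index surgery adjusting for baseline scores". The SAP contains no alpha, multiplicity rule or testing order, and it does not mention the likelihood ratio test. The intervals in eTables 8 to 13 are given as ordinary 95% CIs. The footnote to eTables 9 and 10, the PRO results by sex and by age group, reads "Estimates with 95% confidence intervals not covering zero are bolded".

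**The concern.** A multiplicity adjustment used only to choose the sample size protects nothing. It controls error only if the comparisons are judged at the adjusted level, or in an order that gives the same protection. Here the commitment is made in the sizing section for a named family, and the sections that govern inference never mention it again.

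An analyst who follows the written plan would report pairwise clearance and every overall PRO comparison at the nominal 95% level. A reader of section 6.4 would believe that the error over the whole set is held at 5%. What is at stake is the chance of at least one false claim that one procedure is better than another, mainly on PROs, which involve many scores at four times.

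**Working it through.** **Inputs.** From section 6.4: 80% vs 65% (URS vs SWL), 90% vs 65% (PCNL vs SWL), 80% power, alpha 0.05 before adjustment, 15% loss, and 294/294/92 patients. Assumed: two-sided tests, pooled null variance, and a 1:1 split within each pair.

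**Size of the family.** Three treatment pairs for clearance plus three pairs at four times for PROs gives 3 + 3 × 4 = 15, so the per-comparison alpha is 0.05/15 = 0.00333 (z = 2.935).

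**Reproducing the plan's figure.** n = [z(α/2)·√(2p̄q̄) + z(β)·√(p1q1 + p2q2)]² / (p1 − p2)², then divided by 0.85.

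- 80% vs 65%: [2.935 × 0.6315 + 0.8416 × 0.6225]² / 0.0225 = 251.2, so 252; 252/0.85 gives 297 (printed 294).
- 90% vs 65%: [2.935 × 0.5906 + 0.8416 × 0.5635]² / 0.0625 = 78.0, so 78; 78/0.85 gives 92 (printed 92).

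| Divisor | URS and SWL, each | PCNL |
|---|---|---|
| 1 (alpha 0.05) | 163 | 51 |
| 3 | 218 | 69 |
| 13 | 290 | 91 |
| 15 | 297 | 92 |
| 16 | 299 | 93 |
| Printed | 294 | 92 |

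The printed numbers therefore rest on a Bonferroni alpha. Divisors 13 and 16 also come close, but only 15 matches the listed family.

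**Power under each rule, after 15% loss** (294 × 0.85 ≈ 250; 92 × 0.85 ≈ 78):

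| Comparison | alpha 0.05/15 | alpha 0.05 |
|---|---|---|
| URS vs SWL, 250 vs 250 | 79.7% | 96.6% |
| PCNL vs SWL, 78 vs 78 | 80.0% | 96.9% |
| PCNL vs SWL, 78 vs 250 (printed arms) | 95.5% | 99.8% |

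**Family-wise error when each comparison is read at 5%.**

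- Three clearance pairs: 1 − 0.95³ = 14.3% if independent. Simulation with shared arms (250/250/78, no true differences) gives 11.9%. In the same simulation, gating the pairs on an overall test at 0.05 gives 5.0%.
- Fifteen comparisons: 1 − 0.95¹⁵ = 53.7% if independent. Simulation with equally correlated normal statistics gives about 46% at correlation 0.3 and about 25% at 0.7.

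**An overall table.** eTable 8 compares PCNL with URS at 1 week on eight scores, without subgroups. Taking SE = (upper − lower)/3.92, four of the eight differences exclude zero:

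| Score | Difference (95% CI) | SE | abs(z) | Exceeds 2.935? |
|---|---|---|---|---|
| QUIKSS | −20.7 (−39.8, −1.7) | 9.72 | 2.13 | No |
| Anxiety | −22.4 (−26.2, −18.5) | 1.96 | 11.4 | Yes |
| Sleep Disturbances | −20.5 (−35.1, −5.9) | 7.45 | 2.75 | No |
| Stress Experiences | −18.9 (−24.3, −13.6) | 2.73 | 6.92 | Yes |

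Two of the four remain at 0.05/15. The result depends on the family chosen: over these eight scores alone the limit is 0.05/8 = 0.00625, and Sleep Disturbances (p = 0.0059) would just pass. eTable 8 reports proportions exceeding a threshold and not mean scores, so this is an illustration and not a re-analysis of the planned tests.

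**The case against.** The strongest reply is that the plan is silent in several places, which differs from being explicitly unadjusted. The likelihood ratio test and the PRO models state no level, and a 95% CI for an odds ratio can be a reporting convention and not a decision rule. That stands. A reader might infer that the documents direct every comparison to be judged at an unadjusted 95%, and they do not go that far. The silence still leaves a stated commitment without any implementing text.

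Second, an overall clearance test is planned, and it would protect the three pairs. It would if the pairs depended on it: the simulated error falls from about 12% to 5%. No such condition is written, and it would not cover the PROs. The clearance tables shown contain one pair only (PCNL vs URS), so the 12% describes the protocol's three-pair plan and not those tables.

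Third, the only printed flagging rule is in subgroup tables that the protocol regards as descriptive. This also stands. A reader might count how many intervals in eTables 9 and 10 exclude zero and treat those that fail 0.05/15 as false positives. Subgroup estimates were never in the section 6.4 family, so the count says nothing about the overall comparisons. Bolding still invites a significance reading, which is a matter of labelling.

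Fourth, section 6.2 lists patient experiences as a secondary endpoint, and the study is a cohort, so formal adjustment of PROs could be seen as optional. That would be arguable had section 6.4 not called both aims primary and placed PROs inside the adjusted family.

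**Conclusion.** The point holds as a gap between section 6.4 and the analysis text. The protocol promises Bonferroni control over a named family, the sample size was built on it, and no rule in section 6.3.2 or the SAP delivers it. At a nominal 5% each, the family-wise error is about 12% for three ungated clearance pairs. For 15 comparisons it is 54% if independent, and about 25% to 46% at correlations of 0.7 to 0.3.

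These figures assume two-sided tests and the inferred family of 15. They ignore any effect of weighting and clustering on the variance. That family does not count PRO domains: with the five PROs of the Aim 2 statement it would be 3 + 60 = 63, and more unadjusted tests would raise the error further.

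A reader might also infer that the study is underpowered or that its power claim misleads. The documents do not support that. Testing at a looser level than the one used for sizing raises power to about 97% or more, so the printed 80% is conservative. Nor do the documents show that false PRO claims were made, because they contain no stated conclusions on PROs. The harm is confined to type I error.

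**What to change.** In the SAP Outcome model section:

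1. State the family, its divisor, and whether PRO domains are counted.
2. Make the pairwise clearance comparisons conditional on the overall likelihood ratio test at a stated alpha, or adjust them.
3. Apply the protocol's Bonferroni adjustment, or Holm, to the overall PRO-by-time comparisons.
4. Report adjusted p-values or CIs beside the nominal 95% CIs.

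In eTables 9 and 10, label the results as descriptive and the bolding as nominal. eTable 8 has no flags to change, but its differences should be accompanied by adjusted results.

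The cost is a few lines of SAP text, some relabelling and recomputed intervals, with no new data. The downside is that fewer PRO differences would be called significant.

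### Section 6.4 gives one 80% power for both Aim 1 contrasts, but 92 PCNL patients is an equal-group size; against the 294 SWL patients stated beside it, power is about 96% before weighting

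*Combined protocol and SAP*

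**What the plan says.** Section 6.4 of the protocol (Aim 1) states that "294 patients in SWL, 294 patients in URS, and 92 patients in PCNL will have 80% power". That one figure covers two named differences in stone clearance: 80% for URS against 65% for SWL, and 90% for PCNL against 65% for SWL. The nominal alpha is 0.05 and the sizes are described as "accounting for multiple comparisons and loss to follow-up".

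The same section says "We use Bonferroni adjustment to allow for multiple comparisons, which is known to be conservative" and lists the family as "difference in stone clearance across 3 treatment options and mean difference in PROs across 3 treatment options at 1 week, 3 weeks, 6 weeks, and" (the list ends with the three-month assessment). It assumes 15% loss to follow-up in general, and 10% for Aim 2. It expects unequal groups: "we anticipate enrolling approximately 750 patients in URS, 350 in SWL, and 100 in PCNL".

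It does not state the Bonferroni divisor, the sidedness, the allocation ratio, or power for each contrast. It makes no allowance for precision lost to weighting, although sections 6.3 and 6.3.2 specify a propensity-weighted logistic model for the primary outcome.

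**The concern.** Two contrasts with very different effects (15 and 25 percentage points) and very different group sizes (294 v 294 and 92 v 294) share one power figure. That is unlikely unless each size was worked out separately with equal groups. If so, the size given for PCNL does not belong to the design described in the same sentence.

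PCNL is the scarce group, about 100 of the 1,200 patients expected. A reader of section 6.4 would take 92 as the number at which PCNL–SWL just reaches 80%, and would take the two contrasts as equally powered. Neither is so. The reader also cannot tell how much precision the weighted analysis can lose before either contrast falls below 80%.

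**Working it through.** **Inputs from section 6.4.** Clearance 65% (SWL), 80% (URS), 90% (PCNL); sizes 294, 294 and 92; nominal alpha 0.05 with Bonferroni; 15% loss.

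**Inferred.** Two-sided test. Divisor 15 = 3 pairs × (stone clearance + PROs at 4 time points), so alpha = 0.05/15 = 0.00333 and z = 2.935. For 80% power, z = 0.842.

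**Step 1: reproduce the stated sizes** (pooled two-proportion formula, equal groups).

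n per group = [2.935·√(2p̄(1−p̄)) + 0.842·√(p₁(1−p₁) + p₂(1−p₂))]² / (p₁−p₂)²

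- URS–SWL: p̄ = 0.725. (2.935 × 0.6315 + 0.842 × 0.6225)² / 0.15² = 251.2. Divided by 0.85 this is 295.5, or 297 if 251.2 is first rounded up to 252 (stated: 294).
- PCNL–SWL: p̄ = 0.775. (2.935 × 0.5906 + 0.842 × 0.5635)² / 0.25² = 78.0. Divided by 0.85 this is 91.7, so 92 (stated: 92).

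So 92 is the PCNL size that goes with 92 SWL patients.

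**Step 2: power at the stated sizes.** Evaluable after 15% loss: 294 × 0.85 = 249.9 and 92 × 0.85 = 78.2.

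Power = Φ[(|p₁−p₂| − 2.935·SE₀)/SE₁], with SE₀ the pooled and SE₁ the unpooled standard error.

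| Contrast | Evaluable | SE₀ | SE₁ | z | Power |
|---|---|---|---|---|---|
| URS–SWL | 249.9 v 249.9 | 0.03995 | 0.03938 | 0.832 | 79.7% |
| PCNL–SWL, equal groups | 78.2 v 78.2 | 0.06678 | 0.06372 | 0.847 | 80.2% |
| PCNL–SWL, stated groups | 78.2 v 249.9 | 0.05882 | 0.04540 | 1.704 | 95.6% |

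Simulation (400,000 replicates at 250, 250 and 78) gives 80.0% for URS–SWL, 95.6% for PCNL–SWL and 77.7% for detecting both.

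**Step 3: sensitivity of the 96%.**

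- *Divisor.* With 15% loss, divisors 13 to 16 come close to the stated sizes and give 96.1% to 95.3%. With 10% loss, divisors 20 and 21 also fit (292.3 and 90.8; 294.6 and 91.5) and give 96.0% and 95.8%. Divisors 20 and 21 with the 15% evaluable numbers give 94.4% and 94.2%. The overall range is 94–96%.
- *Test.* At 78 v 250 and divisor 15: 93.5% continuity-corrected, 96.8% by likelihood ratio test (simulated), 96.9% arcsine, 99.5% unpooled.

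**Step 4: weighting.** If weighting leaves a fraction f of nominal size in both groups, both standard errors are divided by √f.

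| f | PCNL–SWL z | PCNL–SWL power | URS–SWL z | URS–SWL power |
|---|---|---|---|---|
| 1.0 | 1.704 | 95.6% | 0.832 | 79.7% |
| 0.8 | (0.25 − 2.935 × 0.06576)/0.05076 = 1.122 | 86.9% | (0.15 − 2.935 × 0.04466)/0.04403 = 0.43 | 67% |
| 0.7 | (0.25 − 2.935 × 0.07030)/0.05426 = 0.804 | 78.9% | (0.15 − 2.935 × 0.04774)/0.04707 = 0.21 | 58% |

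The fractions are illustrative, since the documents give no expected effective size. The URS–SWL column uses the stated 294 v 294, not the larger enrolment anticipated.

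**The case against.** The strongest defence is that the sentence describes one design with one target. URS–SWL is the binding contrast and meets 80% almost exactly; PCNL–SWL exceeds it. Read as power to detect both differences, the figure is also close, at about 78%. No group is too small for a named contrast, and anticipated enrolment (350 SWL, 100 PCNL) exceeds the stated sizes. The rates, sizes, nominal alpha and loss are all given, so most of the surplus can be derived.

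Much of this stands. A reader might infer that the power statement as a whole is wrong, or that the margin was concealed. The documents support neither: the figure is right for URS–SWL, errs on the safe side for PCNL–SWL, and the surplus is simply not stated.

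The defence does not explain the 92. If 80% were meant as a floor for these three groups, 92 would not be the number that meets it; it meets 80% only against 92 SWL patients. The sentence gives no wording of a minimum and no figure by contrast.

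It is also fair to object that 96% describes no planned analysis, because the primary model is weighted. That limits how the figure may be reported, and the fix allows for it.

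**Conclusion.** The point holds as a conservative misstatement for one of the two named contrasts. At the stated sizes PCNL–SWL has about 96% power (94–96% over the fitting divisors), some 16 percentage points above the 80% given; URS–SWL has 80%. This rests on an inferred divisor, a two-sided test, 15% loss, the pooled formula, and unweighted independent observations. That there is a surplus is robust to the divisor and the test; its exact size is not.

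Two further inferences should be resisted.

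- *That PCNL patients can be spared.* Against a full 250 SWL, about 52 evaluable PCNL patients would give 80% for that pair alone, which suggests a tolerable design effect near 1.5. But this holds SWL at its unweighted size, while weighting costs precision in both groups. Power to detect both differences would also fall to about 68%.
- *That the surplus helps PCNL against URS*, the pair in the SAP's result tables. The Aim 1 sentence does not power that pair. For 90% v 80% at 78 v 250 evaluable and alpha 0.05/15, power is about 14%.

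**What to change.** Restate Aim 1 in section 6.4 by contrast, at the allocation actually given:

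- URS–SWL, 294 v 294 (about 250 v 250 evaluable): about 80%.
- PCNL–SWL, 92 v 294 (about 78 v 250 evaluable): about 96%.

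State the Bonferroni divisor, sidedness, loss rate, allocation ratio and test formula used. If the divisor was not 15, recompute both lines. Label the figures as unweighted, and add a short table of power when weighting reduces effective size in both groups; for PCNL–SWL this is about 87% at 80% of nominal and about 79% at 70%. Show URS–SWL in the same table. Do not give 52 as a tolerable PCNL number or quote a design effect of 1.5.

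The cost is one rewritten sentence and a small table. No sample size, test or study procedure changes.

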| PRO                                                                                                                                                                                                                                                                                                                                                                                             | Standard deviation of weighted score of study sample at baseline | The proportion of participants whose difference in the score at 1 week exceeded 50% baseline standard deviation, % (95% CI) |                  |                     |
|-------------------------------------------------------------------------------------------------------------------------------------------------------------------------------------------------------------------------------------------------------------------------------------------------------------------------------------------------------------------------------------------------|------------------------------------------------------------------|-----------------------------------------------------------------------------------------------------------------------------|------------------|---------------------|
|                                                                                                                                                                                                                                                                                                                                                                                                 |                                                                  | PCNL                                                                                                                        | URS              | Difference          |
| DVSS † score                                                                                                                                                                                                                                                                                                                                                                         | 4.38                                                             | 37.6 (12-63.3)                                                                                                              | 29.8 (26.1-33.6) | 7.8 (-18.1,33.7)    |

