### Patient Experiences: Overall Treatment Effect.

For PROMIS measures, we will fit weighted linear mixed effects models to test the difference in T-scores after surgery across treatment options for each domain. Separate models will be built for outcomes at 1 week, 3 weeks, 6 weeks, and 3 months after surgery. We will also take advantage of the longitudinal nature of the PROs and fit WLMMs to compare the slopes of the PROs over time and the area under the curve.

Secondary patient experience outcomes, including number of emergency department visits, unplanned hospitalizations, and surgical retreatment will be compared across treatment options using weighted zero-inflated negative binomial regression models.

**SubAim 2a: HTE.** We will examine for HTE with interaction terms between procedure and patient age and procedure and sex to identify associations that differ for subgroups. We will also explore HTE by other patient participant characteristics including, but not limited to, ambulatory status.

**SubAim 2b: Effect modification by procedure-specific techniques.** We will stratify the data by treatments and, within each treatment; we will fit linear mixed effect models to test whether modifiable techniques are associated with patients' experiences for each procedure.

We will evaluate the change in outcomes across PKIDS after knowledge of best practices generated by the above analyses are integrated into clinical care. Our regression models will test differences in both the intercept (average value) and slope (change over time) for outcomes.

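### Section 6.4, Aim 2: 80% power for a 2-point PRO difference with 39 per group holds only for an unstated SD of about 2 to 3, while the study's PROMIS SDs are 8.47 to 11.80

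*Combined protocol and SAP*

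**What the plan says.** The Aim 2 paragraph of section 6.4 opens with "Minimal important differences for many PROMIS domains are in the range of 2 to 6" and takes the bottom of that range as its target. It then states: "39 patients in each group will have 80% power to detect an expected difference of 2 points in each of the 5 PROs". The conditions attached are "Assuming a 10% loss to follow-up" and a significance level of 0.05 adjusted for multiple comparisons.

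The opening paragraph of 6.4 names Bonferroni as the method. It lists the comparisons as stone clearance across the three treatments and the "mean difference in PROs across 3 treatment options at 1 week, 3 weeks, 6 weeks, and 3-months after surgery", without giving a divisor. It sets a general loss to follow-up of 15%, where Aim 2 uses 10%. It plans about 750 URS, 350 SWL and 100 PCNL patients.

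Under Patient Experiences: Overall Treatment Effect, section 6.3.2 says that the PROMIS analysis tests the "difference in T-scores after surgery across treatment options for each domain". The SAP (Outcome model) adjusts the PRO analyses for the baseline score.

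No planning SD appears in either document. The only PROMIS SDs are in eTable 8, in the column headed "Standard deviation of weighted score of study sample at baseline": 8.47, 9.61, 9.92, 10.20, 10.91 and 11.80 for the six PROMIS scales.

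**The concern.** A difference of 2 points on a scale with an SD near 10 is a standardised difference of 0.2. Thirty-nine patients per group is far too few to detect that with 80% power, even before any multiplicity adjustment. Since the sentence gives no SD, a reader cannot see what it rests on.

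At stake is how a null PRO result is read. Section 6.4 counts patients' experiences among the aims that the sample size serves, and the printed statement suggests ample power for the smallest important difference with 39 per arm. A reader who relied on it could take a non-significant PCNL contrast as evidence against a 2-point difference.

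**Working it through.** **Inputs.** From 6.4: 39 per group, 10% loss, difference 2, power 80%, alpha 0.05, planned arms 750, 350 and 100. From eTable 8: SD 8.47 to 11.80, with 10 as a round middle value. Assumed, because not stated: two-sided tests, a range of divisors, and a baseline correlation r of 0 or 0.7.

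**Step 1. Can the 39 be reproduced?** Evaluable per group: 39 × 0.90 = 35.1, taken as 35. The usual formula is n = 2 × (z_alpha + z_power)² × SD² / difference².

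- SD 2.0, 60 comparisons (3 pairs × 4 times × 5 PROs): 2 × (3.341 + 0.842)² × 4/4 = 35.0; 35/0.9 = 38.9, so 39.
- SD 2.5, 4 comparisons: 2 × (2.498 + 0.842)² × 6.25/4 = 34.9, so 35 evaluable and again 39.

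The figure is reproducible, but only with a very small SD. Solving SD = 2 / [(z_alpha + 0.842) × √(2/35)], where √(2/35) = 0.239:

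| Divisor | Implied SD |
|---|---|
| 1 (unadjusted) | 2/(2.802 × 0.239) = 2.99 |
| 3 | 2.59 |
| 12 | 2.26 |
| 15 | 2.22 |
| 60 | 2.00 |

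**Step 2. Power at 35 per group with the eTable 8 SDs** (noncentral t, two-sided, difference 2):

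| Divisor | SD 8.47 | SD 11.80 |
|---|---|---|
| 1 | 16.4% | 10.8% |
| 3 | 7.7% | 4.6% |
| 12 | 2.8% | 1.5% |
| 15 | 2.4% | 1.2% |

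More favourable variants do not rescue it. All 39 evaluable, one-sided 0.05 and SD 8.47 give 27%. A three-group ANOVA gives 9 to 17%. Baseline adjustment shrinks the SD by √(1 − r²); at r = 0.7 the factor is 0.714 and unadjusted power is 17 to 28%. Reaching 80% needs an SD of 2.99, hence r = √(1 − (2.99/8.47)²) = 0.94 up to √(1 − (2.99/11.80)²) = 0.97.

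**Step 3. What 35 per group can detect, and what 2 points would need.** The detectable difference at 80% power is 2.802 × SD × 0.239, or 5.7 to 7.9 points unadjusted. For 2 points, 282 to 547 evaluable per group are needed unadjusted, and 493 to 957 with a divisor of 12.

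**Step 4. Planned arm sizes less 10%.** 100, 350 and 750 become 90, 315 and 675. Power for 2 points over SD 8.47 to 11.80, before weighting and baseline adjustment:

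| Pair | 0.05 | 0.05/15 |
|---|---|---|
| PCNL vs URS | 33 to 56% | 8 to 20% |
| PCNL vs SWL | 29 to 50% | 6 to 17% |
| SWL vs URS | 70 to 93% | 32 to 70% |

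The detectable difference is (z_alpha + 0.842) × SD × √(1/n1 + 1/n2). The square roots are 0.1122, 0.1195 and 0.0682, and the multipliers are 2.802 at 0.05 and 3.777 at 0.05/15. At SD 10, without weighting, in points:

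| Pair | r = 0, 0.05 | r = 0, 0.05/15 | r = 0.7, 0.05 | r = 0.7, 0.05/15 |
|---|---|---|---|---|
| PCNL vs URS | 3.14 | 4.24 | 2.25 | 3.03 |
| PCNL vs SWL | 3.35 | 4.51 | 2.39 | 3.22 |
| SWL vs URS | 1.91 | 2.58 | 1.37 | 1.84 |

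**Where 15 comes from.** It is inferred: 3 stone-clearance pairs plus 3 × 4 PRO contrasts. With 15% loss, the pooled two-proportion formula at 0.05/15 gives 295.5 and 91.7 for Aim 1, against the plan's 294 and 92. At 0.05/12 it gives 284.6 and 88.3. Fifteen is the closer fit but not an exact one.

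**The case against.** Four points can fairly be made for the plan.

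- **No arithmetic error is shown.** A reader might infer a miscalculation. The documents do not support that: with no SD stated, 39 comes out exactly at SD 2.0 with 60 comparisons. The contradicting SDs are observed baseline values from the results tables, not planning inputs, and they stand in for the post-operative SDs. This stands, and it fixes the nature of the fault as an undisclosed, implausible input. It does not rescue the figure: even the smallest SD in eTable 8 for any measure, 4.38 for the DVSS (a different scale), exceeds 2.99.
- **39 is not the design.** A reader might infer that the whole PRO comparison has 11 to 16% power. That is too broad. Every planned arm exceeds 39, and SWL versus URS has 70 to 93% unadjusted power for 2 points. This stands; the weakness at planned enrolment lies mainly with PCNL.
- **Baseline adjustment helps.** At r = 0.7, unadjusted power for PCNL versus URS at the planned sizes rises to 56 to 84%. That is a real gain, but r is assumed and unlikely to be uniform. The baseline coefficients for PROMIS scales in eTable 9 run from 0.20 to 0.69; they are slopes, not correlations, and are lowest for pain. With a divisor of 15 the detectable difference is still 3.03 points, and weighting pulls the other way.
- **Intervals are already reported.** eTables 8 to 10 give 95% confidence intervals for PRO contrasts, and PROs are the secondary endpoint. Misreading of a null result is therefore a risk, not a certainty.

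It is also tempting to quantify the weighting loss from the width of the PCNL interval in eTable 12. That analysis concerns a binary outcome with weights also corrected for misclassification, so it gives no figure for the PROs.

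**Conclusion.** The Aim 2 power statement is unsupported. It requires an SD of about 2.0 to 3.0, roughly 3 to 6 times below the PROMIS SDs in eTable 8. With those SDs, 35 evaluable per group give about 11 to 16% power unadjusted, although the sentence claims a multiplicity adjustment that would lower this further.

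This rests on two-sided tests and on baseline SDs representing the outcome SDs. The conclusion about the 39 survives every divisor tried and any baseline correlation below about 0.94. The planned-size figures are less firm: they depend on the divisor, on r and on the weighting loss, none of which the plan gives. On those figures SWL versus URS is reasonably placed for 2 points without Bonferroni adjustment, and the PCNL comparisons generally are not.

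**What to change.** Replace the Aim 2 sentence in section 6.4 with one that:

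1. states the SD (about 10, with eTable 8 named as an observed source), the Bonferroni divisor, the sidedness, the assumed baseline correlation, and one loss rate in place of the present 10% and 15%;
2. gives the detectable difference for each treatment pair at the planned sizes, as in the last table under Step 4, for r = 0 and for an assumed r;
3. shows any inflation for inverse probability weighting as a labelled assumption with a range;
4. says that the PCNL comparisons are not powered for 2 points, and that null PRO results are to be read from the confidence intervals.

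The cost is a rewording and a less favourable stated figure. No extra patients and no change to the analysis are needed.
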